**Cardiac Toxicity**

Grade 2 Toxicity

- Suspend treatment and increase the frequency of ECG monitoring until QTc<450 ms.
- Correct any electrolyte imbalances and discontinue any medications that may prolong the QTc interval.
- If toxicity can be restored to Grade 1 or below within 14 days, reduce the dose for treatment and continue to increase the frequency of ECG monitoring; otherwise, treatment should be discontinued, and the subject should exit the study.
- If Grade 2 toxicity recurs, treatment should be discontinued, and the subject should exit the study.

≥ Grade 3 Toxicity

- Treatment should be discontinued, and the subject should exit the study. The subject will receive a consultation from a cardiology specialist.

**Diarrhea**

Inform the subject to closely monitor for symptoms of enteritis (such as diarrhea, abdominal pain, bloody stools, or fever). If diarrhea occurs, it is recommended that the subject drink 8-10 cups of clear water daily to stay hydrated. Antidiarrheal medication (such as loperamide) may be administered until symptoms resolve. If diarrhea persists for more than 48 hours, consideration should be given to administering prophylactic antibiotics.

Grade 3 Toxicity

- Upon first occurrence of Grade 3 toxicity, treatment should be suspended, and antidiarrheal medications should be administered until toxicity resolves to Grade 1 or below. Once resolved, the medication can be resumed at the originally planned dose.
- If, after resuming treatment, Grade 3 toxicity occurs again, treatment should be suspended, and antidiarrheal medications should be administered until toxicity resolves to Grade 1 or below. Upon resolution, the dose should be reduced to the previous level.

Grade 4 Toxicity

- Upon first occurrence of Grade 4 toxicity, treatment should be suspended, and antidiarrheal medications should be administered until toxicity resolves to Grade 1 or below. Once resolved, the dose should be reduced to the previous level.
- If, after resuming treatment, Grade 4 toxicity occurs again, treatment should be discontinued, and the subject should exit the study.

**Nausea/Vomiting**

If the subject experiences vomiting symptoms for the first time, antiemetic medications may be administered for treatment.

Grade 3-4 Toxicity

- Upon first occurrence of Grade 3 or 4 toxicity, treatment should be suspended, and antiemetic medications should be administered until toxicity resolves to Grade 1 or below. Once resolved, the medication can be resumed at the originally planned dose, and it is recommended to use antiemetics as a preventive measure before dosing.
- If, after resuming treatment, Grade 3 or higher toxicity occurs again, treatment should be suspended, and antiemetic medications should be administered until toxicity resolves to Grade 1 or below. Upon resolution, the dose should be reduced to the previous level.

# Data Management

This trial employs electronic data management using DAS for EDC (V6.0). The main data management processes are outlined below, with further details available in the Data Management Plan (DMP).

The DMP, which serves as the guiding document for data management, is written by the Data Manager (DM) and approved by the sponsor. Data management activities will be conducted according to the timelines, content, and methods defined in the DMP.

## EDC Data Management

- Electronic Case Report Form (eCRF): The data manager designs and constructs the eCRF based on the study protocol and sets logical checks according to the Data Verification Plan (DVP). After testing and obtaining approval from the sponsor, the eCRF is released for use.
- Data Entry: eCRF data is sourced from original records. Data entry personnel enter the subject visit data into the Electronic Data Capture (EDC) system in a timely manner, following the eCRF completion guidelines.
- Source Data Verification (SDV): Monitors verify the consistency between eCRF data and source data. Any discrepancies may lead to queries.
- Data Queries and Responses: Queries arise from system-generated questions during EDC logical checks, as well as from manual queries by monitors and data managers. Researchers are required to respond to queries in a timely manner. Data managers and monitors will address the queries, and if necessary, additional queries may be issued until the data is deemed "clean."
- Investigator Signature: After data entry is completed and Source Data Verification (SDV) is performed, the investigator conducts an electronic signature review for confirmation. If there are any data revisions after signing, a new signature is required.
- Database Locking: The database lock record is signed by the principal investigator, the sponsor, the statistical analysts, and the data management personnel. Following this, the data manager locks the database.
- Database Submission: The data manager submits the database to the statistical personnel.
- eCRF Archiving: A PDF electronic document of the eCRF for each subject is generated and saved.
- Data Management Report: A report is written by the data manager.
- EDC Closure: After the statistical analysis is completed, the data manager closes the database.

## External Data Transfer

Sign the external data transfer agreement and manage external data according to the Data Management Plan (DMP).

## Medical Coding

Adverse events are coded using the MedDRA dictionary (version 22.0 or above), while concomitant medications are classified using the latest version of the WHO ATC classification.

# Statistical Analysis

## Analysis Dataset

**Safety Analysis Set (SS)**

The safety analysis population is defined as all patients who received at least one dose of the investigational drug and have at least one safety assessment data point. The SS set is the dataset used for the safety analysis.

**Full Analysis Set (FAS)**

All participants who entered this study and received at least one dose of the investigational drug, along with at least one efficacy assessment data point excluding baseline, will be included in the FAS (Full Analysis Set).

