## Criteria for Withdrawal from the Study

Participants have the right to withdraw from the study at any stage, and their interests will not be adversely affected by their decision to exit. If a participant requests to withdraw from the trial, study treatment must be discontinued. Additionally, if a participant does not explicitly state their intention to withdraw but ceases to take medication and undergo tests, this will also be considered a withdrawal or dropout.

If a participant decides to withdraw, all observations should be completed and reported as thoroughly as possible before exiting. A full final assessment should be conducted at the time of withdrawal, and the reason for withdrawal must be documented. If a participant withdraws due to adverse events or abnormal laboratory results, relevant details must be recorded in the case report form.

The investigator should consider early termination of the study for a participant in the event of any of the following occurrences:

1. Evidence of disease progression;
2. Appearance of intolerable toxicity leading to discontinuation of the study drug, and failure to recover within 14 days after discontinuation;
3. Poor compliance by the participant, making them unsuitable to continue in the study;
4. Serious violations of the study protocol that affect drug tolerance and safety evaluation;
5. Participant lost to follow-up;
6. Pregnancy;
7. Other reasons deemed by the investigator as making the participant unsuitable to continue in the trial.

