## Subject Supplementation

Subjects who discontinue the study within 25 days after the first dose for reasons other than dose-limiting toxicities (DLTs) — such as participant withdrawal from the clinical trial, serious protocol violations, failure to meet inclusion/exclusion criteria, poor compliance, or early evidence of disease progression — may be supplemented to ensure that the number of evaluations for DLTs remains sufficient.

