- M Protein Testing: Conducted only for patients with multiple myeloma, including: (1) serum protein electrophoresis (Albumin, Alpha 1, Alpha 2, Beta 1, Beta 2, Gamma, M-spike); (2) immunofixation electrophoresis (IgG, IgA, IgM, light chain types); (3) β2-microglobulin (β2-MG); (4) serum immunoglobulin quantification (serum IgG, serum IgA, serum IgM, serum kappa light chains, serum lambda light chains, kappa/lambda ratio); D25 examination once.
- 12-Lead Electrocardiogram: PR interval, QRS duration, QT interval, QTc interval; assessments at 2 hours and 6 hours after administration on D8, and before and after administration on D11 and D15 (2 hours and 6 hours post-dose), and once on D25.
- Echocardiogram: Performed if symptoms of cardiac abnormalities such as precordial pain or palpitations occur, or if the investigator deems it necessary.
- Imaging Studies: CT or PET-CT or whole-body X-ray examination conducted once on D25; lymphoma subjects will undergo CT or PET-CT, while multiple myeloma patients will undergo X-ray examination (the investigator will determine if additional localized CT is needed); for leukemia subjects, the need for examination will be determined by the investigator based on clinical circumstances.
- Bone Marrow Examination: Determined by the investigator based on clinical needs, including: (1) bone marrow cytology smear classification; (2) bone marrow biopsy + immunohistochemistry; (3) flow cytometry; for leukemia patients, bone marrow examination will include only the bone marrow smear and flow cytometry; D25 examination once.
- Efficacy Assessment: Efficacy will be assessed on D25.
- Compliance Assessment: Patient compliance will be assessed on D25.
- Observation and Recording of Adverse Events.
- Record of Concomitant Medications.

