## End of Study/Early Withdrawal from the Trial

- Vital Signs: Including temperature, heart rate, respiratory rate, and blood pressure (systolic and diastolic).
- Physical Examination: Including assessments of skin, mucous membranes, lymph nodes, head, neck, chest, abdomen, spine/extremities, and neurological system.
- ECOG Performance Status.
- Laboratory Tests:
- Complete Blood Count (CBC): Red blood cell count, hemoglobin, platelet count, white blood cell count, neutrophil count, lymphocyte count.
- Urinalysis: Urine protein, urine red blood cells, urine white blood cells.
- Blood Biochemistry: Serum creatinine, urea, total bilirubin, alanine aminotransferase (ALT), aspartate aminotransferase (AST), alkaline phosphatase, total protein, albumin, electrolytes (K+, Na+, Ca2+, Mg2+, Cl-), total cholesterol, low-density lipoprotein (LDL), high-density lipoprotein (HDL), creatine kinase (CK), creatine kinase-MB (CK-MB), alpha-hydroxybutyrate dehydrogenase (α-HBDH), lactate dehydrogenase (LDH), fasting blood glucose.
- Coagulation Function Tests: Prothrombin time (PT), activated partial thromboplastin time (APTT), thrombin time (TT), fibrinogen (FIB).
- M Protein Testing: Includes: (1) Serum protein electrophoresis (Albumin, Alpha 1, Alpha 2, Beta 1, Beta 2, Gamma, M-spike); (2) Immunofixation electrophoresis (IgG, IgA, IgM, light chain types); (3) Beta-2 microglobulin (β2-MG); (4) Serum immunoglobulin quantification (serum IgG, serum IgA, serum IgM, serum kappa light chain, serum lambda light chain, kappa/lambda ratio); this test is performed only for participants with multiple myeloma.
- 12-Lead Electrocardiogram (ECG): PR interval, QRS interval, QT interval, QTc interval.
- Echocardiogram: Conducted if there are symptoms of cardiac abnormalities such as precordial pain or palpitations, or if deemed necessary by the investigator.
- Urine or Serum Pregnancy Test.
- Imaging Studies (CT or PET-CT or Whole-Body X-ray): CT or PET-CT is performed for lymphoma participants, while X-ray is conducted for multiple myeloma patients (local CT may be added at the investigator's discretion). The decision for imaging in leukemia participants will be made by the investigator based on clinical circumstances.
- Bone Marrow Examination: (1) Bone marrow cytology smear classification; (2) Bone marrow biopsy with immunohistochemistry; (3) Flow cytometry; for leukemia patients, only bone marrow smears and flow cytometry will be performed.
- Efficacy Assessment.

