## Efficacy Evaluation

- Objective Response Rate (ORR): Defined as the proportion of patients whose tumor volume has decreased to a predetermined value and maintained for a minimum required duration. ORR is generally defined as the sum of complete response (CR) and partial response (PR).
- Progression-Free Survival (PFS): The time from the start of patient enrollment until the occurrence of objective tumor progression or death.
- Disease Control Rate (DCR): Refers to the proportion of patients whose tumors have either decreased or stabilized for a certain period, including cases of complete response (CR), partial response (PR), and stable disease (SD).

The efficacy evaluation correspondence for this trial is referenced in the table below. For other diseases not specified in the table, the investigator will determine efficacy based on the latest evaluation criteria for that disease:

| Disease Names | Efficacy Evaluation Criteria |
| --- | --- |
| B-cell Lymphoma  T-cell Lymphoma | ORR =CR+PR+MR  DCR= CR+PR+MR+SD |
| Multiple Myeloma | ORR =sCR+CR+VGPR+PR+MR |
| B-cell Acute Lymphoblastic Leukemia  T-cell Acute Lymphoblastic Leukemia | ORR= CR+CRi  This disease is not applicable for DCR analysis. |
| Other Relapsed or Refractory Hematologic Malignancies | For diseases not defined in this trial, the determination will be based on the clinical researcher's judgment according to the efficacy evaluation guidelines for each disease. |

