## Clinical Efficacy Analysis

- Use FAS Analysis:
- Objective Response Rate (ORR): Calculate the ORR and its 95% confidence interval.
- Disease Control Rate (DCR): Calculate the DCR and its 95% confidence interval.
- Progression-Free Survival (PFS): The time from the start of the study to the date of the first recorded progression (PD) or death, whichever occurs first; if no disease progression is observed, the cutoff date should be the date of the last tumor measurement. PFS will be summarized using Kaplan-Meier plots, and the rates of censoring, quartiles, and their 95% confidence intervals will be listed, along with estimates of progression-free survival rates at different time points and their 95% confidence intervals.

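### The full analysis set excludes dosed subjects who have no post-baseline efficacy assessment, so unassessed subjects leave the ORR and DCR denominators and unassessed early deaths are lost from PFS

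*Protocol*

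**What the plan says.** Protocol section 10.1 sets two conditions for the full analysis set (FAS): at least one dose of study drug, "along with at least one efficacy assessment data point excluding baseline, will be included in the FAS". Section 10.6 opens with "Use FAS Analysis" and lists ORR, DCR and PFS beneath it. The protocol names no other efficacy set and has no rule for a dosed subject without an assessment.

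The first scheduled post-baseline assessment is in section 6.3: "Efficacy will be assessed on D25". Two provisions reach subjects who leave earlier. Section 4.6 states: "A full final assessment should be conducted at the time of withdrawal, and the reason for withdrawal must be documented". Section 6.5 lists an efficacy assessment, imaging and marrow examination at the early-withdrawal visit, and the general flowchart marks efficacy evaluation there as mandatory.

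Section 7.5 defines PFS as "The time from the start of patient enrollment until the occurrence of objective tumor progression or death". Section 10.6 likewise takes whichever of progression and death comes first, and censors subjects without progression at their last tumour measurement. Section 7.5 and appendix 14.6 exclude acute lymphoblastic leukaemia (ALL) from the DCR analysis.

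**The concern.** Entry to the FAS depends on something that happens after treatment starts. The subjects who fail the condition are those who died, were lost, or stopped without a final assessment, and none of them can be recorded as a response or as disease control. Removing them shortens the denominator and leaves the numerator alone, so any error runs in the drug's favour.

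For PFS the set also conflicts with the endpoint. Death is an event in sections 7.5 and 10.6, yet a subject who is dosed and dies before any assessment is not in the set on which PFS is computed. Section 3.4 makes any grade 5 adverse event a DLT, so the same death could count against the dose in the DLT analysis and be absent from PFS.

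At stake is the preliminary efficacy picture, a secondary purpose in section 2.2. Dose escalation does not depend on it.

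**Working it through.** **Inputs from the protocol.** Seven dose groups of 3 to 6 subjects: 7 × 3 = 21 and 7 × 6 = 42, which reproduces the planned enrolment of 21–42 in section 4.1. The protocol states no expected ORR, DCR or PFS and no early-loss rate.

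**Assumed inputs.** The number of responders, the number with disease control, and the number m of dosed subjects with no post-baseline assessment.

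**Who is excluded**

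| Subject | Post-baseline assessment | In the FAS? |
| --- | --- | --- |
| Reaches D25 and is assessed | yes | yes |
| Leaves before D25, assessed at the early-withdrawal visit | yes | yes |
| Leaves or is lost before D25, not assessed | no | no |
| Dies before any assessment | no | no |

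**ORR.** All dosed: r/N. FAS: r/(N − m). The ratio is N/(N − m). With r = 10 and N = 42 (exact 95% limits, chosen here for illustration):

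- m = 0: 10/42 = 23.8% (12.1 to 39.5)
- m = 2: 10/40 = 25.0%, factor 42/40 = 1.05
- m = 4: 10/38 = 26.3% (13.4 to 43.1), factor 42/38 = 1.105
- m = 8, an extreme case: 10/34 = 29.4% (15.1 to 47.5)

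At N = 21 the factor is 21/20 = 1.05 for m = 1, 21/18 = 1.17 for m = 3 and 21/15 = 1.40 for m = 6. In a single dose group of three with one responder, one unassessed subject turns 1/3 into 1/2.

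**DCR.** The formula is the same, with N counting dosed subjects without ALL. With 10 controlled among 21: 10/21 = 47.6%; m = 1 gives 10/20 = 50.0%; m = 3 gives 10/18 = 55.6%.

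**PFS, unassessed deaths.** Let d be the number of deaths before any assessment. If nobody is censored before them, the curve for all dosed subjects equals the FAS curve multiplied by (N − d)/N once those deaths have occurred. Considering these subjects alone, PFS at D25 is:

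| N | d | All dosed | FAS |
| --- | --- | --- | --- |
| 42 | 2 | 40/42 = 95.2% | 100% |
| 42 | 4 | 38/42 = 90.5% | 100% |
| 21 | 3 | 18/21 = 85.7% | 100% |

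A later FAS estimate of 40% would be 40 × 40/42 = 38.1% with d = 2 of 42, and 40 × 38/42 = 36.2% with d = 4.

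**PFS, subjects who leave alive and unassessed.** They have no tumour measurement after baseline, so the censoring rule places them at the time origin, where they contribute to no later risk set. A small Kaplan-Meier example with and without two such subjects gave identical curves.

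**The case against.** The strongest reply is that the protocol already limits the loss. A reader might infer that everyone who leaves before D25 disappears from the efficacy analysis. That is not so: the FAS asks for any post-baseline assessment, not the D25 visit, and sections 4.6 and 6.5 and the flowchart require one at early withdrawal. Withdrawal for progression will normally rest on such an assessment. This part of the objection stands. It does not reach subjects who die or are lost, or those whom section 4.6 treats as dropouts because they stop both drug and tests.

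Three other strong readings also fail:

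- **Every early exit inflates PFS.** Only unassessed deaths do, or a progression never recorded as an assessment.
- **Replacement under section 4.7 enlarges the bias.** Replacements "may be supplemented to ensure that the number of evaluations for DLTs remains sufficient". Drawn from the same population and subject to the same FAS rule, they leave the expected inflation factor unchanged.
- **Discretionary imaging makes the loss worse in leukaemia.** The flowchart notes base leukaemia response mainly on marrow smears. The wording on marrow timing is mixed, but section 6.3 lists a D25 examination.

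Eligibility also works against early death: expected survival of at least 12 weeks (84 days) is more than three times the 25-day window. Finally, the shift with 2 to 4 of 42 unassessed lies well inside the confidence interval, the analysis is mainly descriptive, and no efficacy threshold is set. All this bears on the size of the problem. It does not remove the direction of the bias or the conflict with the PFS definition.

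**Conclusion.** The point holds in limited form. As written, the plan removes dosed subjects with no post-baseline efficacy assessment from all three efficacy analyses. This can never lower ORR, or DCR outside ALL, and raises any non-zero rate by N/(N − m). PFS is overstated only through deaths before any assessment (or progressions never recorded as one), which the protocol itself defines as events.

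The effect is probably small overall: about 1 to 2.5 percentage points of ORR for 2 to 4 unassessed of 42, assuming 10 responders. It can be larger within a dose group of 3 to 6. These sizes rest on assumed losses and response counts. The direction follows from the definitions alone. The statistical analysis plan was not available, but the analysis set and its use are fixed in the protocol. DLT and MTD conclusions are unaffected.

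**What to change.** In sections 10.1 and 10.6:

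- Analyse ORR, DCR and PFS in all subjects who received at least one dose.
- Count subjects with no post-baseline assessment as non-responders for ORR and as not controlled for DCR, keeping the ALL exception for DCR.
- Count death before the first assessment as a PFS event on the date of death.
- Censor subjects who leave alive and unassessed at day 1.
- Keep the present FAS as a response-evaluable set for sensitivity analysis, and report how many dosed subjects it leaves out in each dose group, with reasons.

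The cost is a few sentences and no new data collection. ORR and DCR will come out slightly lower if any subject is unassessed, and early PFS lower if any unassessed subject died.

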**Pharmacokinetic concentration Set (PKCS) :**

All enrolled participants in this study have received at least one dose of the investigational drug and have at least one valid concentration data point for the active ingredient after treatment during the trial period.

**Pharmacokinetic Parameter Set (PKPS):**

All participants enrolled in this study have received at least one dose of the investigational drug and have at least one valid pharmacokinetic (PK) parameter during the trial period. Participants who have serious protocol violations that impact the PK parameter results will not be included in the PK Population Set (PKPS).

**DLT Analysis Set**

The DLT analysis set includes participants who received at least 80% of the planned dosage within 21 days after the first dose, or who experienced a DLT after receiving at least one dose. This analysis set will be used for the analysis and summary of DLT events.

